# Study protocol of a randomised controlled trial to examine the impact of a complex intervention in pre-frail older adults

**DOI:** 10.1007/s40520-018-1106-7

**Published:** 2019-01-02

**Keywords:** Frailty, Nutrition, Physical activity, Older adults, Cost effectiveness

## Abstract

**Background:**

Frailty is a multidimensional geriatric syndrome associated with functional loss. The Senior Chef (SC, nutrition) and SAYGO (strength and balance exercise) programmes are well accepted among older adults but the impact of each, or a combination of both, on the frailty syndrome in pre-frail older adults is unknown.

**Aims:**

To determine the effectiveness and cost-effectiveness of a complex intervention consisting of the SC and/or SAYGO programmes to prevent progression of frailty in pre-frail older adults.

**Methods:**

A multi-centre randomised controlled assessor-blinded study. The four intervention groups are SC, an 8-week nutrition education and cooking class; SAYGO, a 10-week strength and balance exercise class; SC plus SAYGO, and a social group (Control). Community-dwelling adults aged 75+ (60 + Māori and Pasifika) in New Zealand are recruited through health providers. Participants are not terminally ill or with advanced dementia, and have a score of 1 or 2 on the FRAIL questionnaire. Baseline assessments are completed using standardised questionnaires prior to randomisation. Four follow-up assessments are completed: immediately after intervention, 6, 12 and 24 months post-intervention. The primary outcome is frailty score, secondary outcomes are falls, physical function, quality of life, food intake, physical activity, and sustainability of the strategy. Study outcomes will be analysed using intention-to-treat approach. Cost analyses will be completed to determine if interventions are cost effective relative to the control group.

**Discussion:**

This trial is designed to be a real world rigorous assessment of whether the two intervention strategies can prevent progression of frailty in older people. If successful, this will generate valuable information about effectiveness of this nutrition and exercise strategy, and provide insights for their implementation.

**Trial registration:**

Australian and New Zealand Clinical Trials Registry number—ACTRN12614000827639.

## Background

Frailty is a precursor to functional loss [1]. It is a multidimensional geriatric syndrome involving several inter-related physiological systems described as a reduction in reserve to meet homeostatic challenge, meaning frail older people are vulnerable to poor outcomes [2] including increased risk of falls, impaired cognitive function, worsening disability, hospitalisation, residential care admissions and mortality [3]. Up to 17% of community-dwelling older people aged 65 + have been reported as frail with 42% pre-frail [3, 4]. In octogenarians, over 60% have been reported to be pre-frail [5].

In the pre-frail state, an older person has homeostatic mechanisms to respond to external stressors, but less than those who are not frail. This transition phase may provide a window of opportunity to prevent deterioration of health outcomes and to maintain quality of life.

Several strategies have attempted to reduce frailty to improve outcomes, with physical activity and nutrition being the most commonly tested interventions [6]; however, results are inconsistent and a greater focus on prevention is needed to reduce the poor outcomes associated with frailty.

Older people are vulnerable to poor nutritional status [7] and inadequate food intake is related to pre-frailty and frailty [8]. Supplements increase weight, particularly in those with malnutrition [9] but the impact of supplements on frailty is uncertain and their wider implementation may be costly. In the InCHIANTI study, 700 + older people, mean age 73 years, adherence to a healthier dietary pattern was associated with a lower risk of being frail over 6-year follow-up [10]. Self-preparation of meals stimulates appetite and is associated with intake of more nutritious meals [11]. Cooking also involves physical and social skills (e.g. shopping for ingredients) and cognitive abilities [11]. Senior Chef (SC) is a programme developed in New Zealand to increase knowledge and practical skills in shopping, cooking and general nutrition for older people. The programme has been evaluated [12] but impact on health outcomes is uncertain.

Physical inactivity increases with age [13]. In New Zealand, after the age of 75 years, approximately 30% men and 40% women were physically inactive, i.e. doing less than 30 min of physical activity per week [14]. Studies in older adults have shown that physical activity interventions improve participation in ‘life’ [15] and this may be through improved physical function, including better flexibility, and cardiorespiratory and muscle fitness particularly in frail older adults [16]. Physical activity trials have had some success in changing lifestyle [17–20] but there is no widespread implementation of programmes for frail and pre-frail older people in New Zealand, with Māori neglected almost completely. Exercise needs to be sustainable for ongoing benefit. The Steady As You Go (SAYGO) programme is a group-based exercise, and was developed from the Otago Exercise Programme set of exercises that has been proven to prevent falls [21]. SAYGO uses a peer-led model, with the group led by a trained facilitator and then transitioning to peer leadership, a model shown to be acceptable and sustainable [22]. The SAYGO programme has been shown to decrease injurious falls [23] and enhance social capital in older adults [24].

According to the Fried criteria, the frailty phenotype includes weight loss, poor endurance and energy, slowness, weakness and low physical activity [25]. Energy and nutrient intake must balance physical activity to maintain a neutral energy expenditure to maintain weight. Furthermore, adequate nutrients are essential for musculoskeletal function. Integrating nutrition and physical activity may be more important in frail/pre-frail than robust older adults to restore an optimal homeostatic mechanism.

Considering the nutrition and exercise focus of the SC and SAYGO programmes, respectively, these have the potential to reverse or slow the progression of frailty in pre-frail older adults using interventions that are acceptable to older adults. Sustainability of these programmes is not only driven by peer leaders but also the availability of funding. For older persons, and health care and service providers, the “value for money” of the intervention is the main interest. For healthcare funders, it is a priority to explore avenues to reduce healthcare costs with the ageing population. The effectiveness and cost-effectiveness the SC and SAYGO programmes to prevent frailty will be determined in this intervention study.

## Methods

This trial aims to determine the effectiveness and cost-effectiveness of the SC and/or SAYGO programmes to prevent frailty in pre-frail older adults.

Design: A multi-centre randomised controlled, assessor-blinded, 2 × 2 factorial study.

Setting and characteristics of participants: Community-dwelling older adults aged 75+ (60 + Māori and Pasifika) across four sites in both the main islands of New Zealand (North and South Islands), with no upper age limit. Māori are the indigenous Polynesian people of New Zealand and Pasifika people are migrants from the South Pacific Region who are living in New Zealand. Health inequalities between the Māori/Pasifika and non-Māori/non-Pasifika are evident [26] and Māori/Pasifika people have lower life expectancy than non-Māori/Pasifika [27], so that applying uniform eligibility criteria would exclude Māori and Pasifika older people.

### Recruitment

Participants are recruited by a mailed invitation signed by the general practitioner (GP) or through Māori health providers (who deliver health and disability services using a cultural framework distinctive to Māori people) by phone or personal invitation from the provider. In New Zealand, 93% of the population are enrolled with a general practice. Practices and providers peruse a list of all enrolled age and ethnicity eligible patients prior to the postal invitation. Eligibility criteria includes not being terminally ill or having advanced dementia as judged by the GP or Māori health provider, living in the community, able to stand, medically safe to participate in low-intensity exercise, and able to use the kitchen utensils safely. Pre-frail status is ascertained using the FRAIL questionnaire [28, 29] (by a score of 1 or 2). The postal pack including the invitation letter and study information along with the FRAIL questionnaire, a reply card, and a reply prepaid envelope is sent to potential participants to facilitate interest and willingness to participate. Those not returning the reply card are contacted by research staff in practices comfortable with this contact for their patients. Eligible older adults giving written informed consent are enrolled in the study. The study was approved by the Southern Health and Disability Ethics Committee, Ministry of Health, New Zealand (Ref 14/STH/101/, 13th August 2014).

### Interventions

After participants complete baseline assessments, they are randomly assigned to one of four groups: SC, SAYGO a group strength and balancing exercise, both SC and SAYGO, and social group (control group).

**Senior Chef** is a weekly 3-h session run for 8 weeks by a trained facilitator following set lesson plans. The 3-h session comprises a morning tea (or light snack) prepared by the facilitator, nutrition education, cooking together (hands-on cooking in pairs) using provided utensils and cooking facilities and then sharing the meal cooked that day. The nutrition education covers practical information about sourcing food, menu planning, budgeting and shopping tips and written information is provided to attendees to take home. After completion of the 8-week programme, the group is encouraged to continue to meet as peers as coordinated by the facilitators.

SAYGO (Steady As You Go) is a weekly 1-h session of exercises to strengthen lower limb muscles and to challenge balance for 10 weeks led by a professionally trained facilitator. The exercises are based on the Otago Exercise Programme, one proven to reduce falls and be sustainable [30]. The programme was adapted for group delivery by physiotherapists and found to be effective in improving physical function in those who participate [22]. During the first 6 weeks, potential peer leader(s) are encouraged by the professionally trained facilitator to consider being a peer leader. Other participants in the group are encouraged to support the peer-led class by helping arrange and set up the venue, collect gold coin donations and take attendance. At week 9, peer leaders are invited to take the class in their community and go through a 1-day training. The training includes a physiotherapy-developed manual and covers class safety, fall prevention, specific exercise routines and first aid workshop. There is a CD with all the exercises that peer leaders use to teach their class to maintain fidelity. The peer leaders and class members decide on the venue for the classes, and continue to meet weekly.

Social group (control) is a weekly 1–2-h “seated” (i.e. non-physical in nature) socialising group facilitated in the local community for 10 weeks. Following the 10-week period, participants are encouraged to continue to attend social groups.

In the trial, attendance sheets are maintained throughout the programmes (by the trained facilitators) and subsequent classes (by the facilitators or peer leaders); no exercise diary or daily dietary intake will be recorded. Transport arrangement is facilitated or provided (if required). Where possible, the facilitators encourage shared rides and source available low-cost travel.

### Outcome measures

Primary outcome: Changes in frailty score. The definition of frailty, adapted from Fried et al. [25] is defined as the presence of three or more of the following characteristics: weight loss, weak grip strength, poor endurance/exhaustion, low physical activity, and slow gait speed.

Weight is measured using Tanita BC-545N scale to the nearest 0.1 kg. Those with ≥ 5% of weight loss in the prior year (by direct measurement of weight) are considered to have weight loss. Weight loss at baseline is determined using the question from FRAIL questionnaire “Have you lost weight in the past 12 months without trying to?” A response of “Yes and loss more than 3 kg/0.5 stones/7 pounds” is considered to indicate ‘weight loss’.Grip strength is determined using the Takei digital handgrip dynamometer Grip D on both hands in a standing position. A grip strength of < 30 kg for men and < 20 kg for women is considered as having weakness [31].Gait speed is determined using the 3-m walk measured with a measuring tape and timed with a stopwatch, conducted in a place with enough space to ensure at least 1 m before and after the 3-m timed allotment. A cut-off of < 0.8 ms^−1^ is considered as having a slow gait speed [32].Exhaustion is determined using a question from the FRAIL questionnaire “How much of the time during the past 4 weeks did you feel tired?” 1 = all of the time, 2 = most of the time, 3 = some of the time, 4 = a little of the time, and 5 = none of the time. Responses of “1” or “2” are considered as having exhaustion, and all others as not [33].Physical activity is determined using the Community Healthy Activities Model Program for Seniors—CHAMPS Activities Questionnaire [34, 35]. Those who reported less than 150 min of moderate intensity activity per week on the CHAMPS questionnaire are considered to have a low physical activity. This estimate is derived from the New Zealand Ministry of Health current physical activity recommendations for older adults of at least 30 min of aerobic physical activity for 5 days each week [14].

Secondary outcomes: falls and physical function

A fall will be defined as “an unexpected event in which the participant comes to rest on the ground, floor, or lower level”, as per guidelines published by the Prevention of Falls Network Europe (ProFaNE) [36]. In ascertaining falls at baseline, participants will be asked “In the previous 12 months, have you had any fall including a slip or trip in which you lost your balance and landed on the floor or ground or lower level?” Falls will be recorded prospectively by the participant using a fall calendar where the participant marks daily if they had a fall. The monthly fall calendar will be returned to the University of Auckland in provided prepaid postage envelopes. Telephone interview by an interviewer blinded to group allocation will be carried out to ascertain further details of falls and injuries, and to follow-up with participants if the monthly fall calendar is not received or to rectify missing data. A blinded medically trained assessor will examine all fall reports to ensure a defined fall has occurred and establish the presence of injury. Injury will be categorised as absent if none recorded, mild to moderate for report of pain, inability to perform usual activities after the fall, bruising, and contusions. Severe injury is any fracture (excluding finger fracture) or any admission to hospital overnight. Rate of falls, risk of falls, and time to first fall will be reported as recommended by Lamb et al. [36].

The validated short physical performance battery (SPPB) will assess physical performance [37]. The SPPB is an objective assessment tool for evaluating lower extremity functioning in older persons. It consists of three parts: the Balance Test, the Gait Speed Test, and the Chair Stand Test, and it can be administered in approximately 10 min. It has a score between 0 and 12 points, the higher the score the better the physical performance. The SPPB is a widely used measure of physical performance for it is practical and safe to be administered by trained assessors in home setting [38].

Functional status will be assessed using the Nottingham Extended Activities of Daily Living (NEADL), a commonly used instrument for assessing activities of daily living within four categories: mobility, kitchen activities, domestic activities and leisure activities. It has a score between 0 and 22, the higher the score the better the functional status [39, 40].

Health-related quality of life will be assessed with the Short Form (SF-12) including the summary scores for physical and mental health-related QOL [41]. Individual-level responses from the SF-12 can be translated into a preference-based quality of life measuring health on a utility scale where ‘dead’ scores 0 and ‘full health’ scores 1. These repeated individual utilities can be used to construct QALYS [41] by plotting time against quality of life and identifying the area under the plotted curve. This QALY measure identifies health over a period of time and is used in the cost-effectiveness analysis.

Process outcomes will also be used as secondary outcomes, namely food intake and reduced sedentary time. Food intake will be assessed using the INTAKE24, an online dietary tool developed by a team in Newcastle University, Newcastle upon Tyne, UK [42]. INTAKE24 is based on the 24-h multiple-pass recalls (MPR) dietary assessment with the New Zealand FOODfiles 2016 database incorporated into the programme. The MPR protocol is suitable for use in the general [43] and oldest old population and matches that used in the Newcastle 85+ and LiLACS NZ studies [44, 45]. Two 24-h MPR will be completed on two separate days (a weekday and a weekend) by a trained interviewer at the participants’ residence or a venue suitable for them.

Physical activity will be determined using the CHAMPS Activities Questionnaire. CHAMPS is a validated questionnaire to measure sedentary (1 METs), low-light (> 1 and ≤ 2 METs), high-light (> 2 and < 3 METs), moderate-to-vigorous physical activity (MVPA, ≥ 3 METs), and total activity in older people over a 4-week period [34, 35].

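### The weight-loss item of the primary frailty score is defined differently at baseline and at follow-up, so change from baseline and the time profile mix true change with a change of instrument

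*Protocol article*

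**What the plan says.** The protocol article, Outcome measures, sets "Primary outcome: Changes in frailty score". The score counts five criteria, one of which is weight loss.

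That section gives two rules for weight loss:
- **General rule:** at least 5% "of weight loss in the prior year (by direct measurement of weight) are considered to have weight loss". No condition on intent is stated.
- **Baseline rule:** "Weight loss at baseline is determined using the question from FRAIL questionnaire". The question is "Have you lost weight in the past 12 months without trying to", and the answer "Yes and loss more than 3 kg/0.5 stones/7 pounds" counts as positive.

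Because baseline is the only exception, the measured rule is the follow-up rule.

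On timing, the Interventions section says "After participants complete baseline assessments, they are randomly assigned to one of four groups". Senior Chef "is a weekly 3-h session run for 8 weeks by a trained facilitator following set lesson plans"; SAYGO and the social group run for 10 weeks. The Abstract places the four follow-ups "immediately after intervention, 6, 12 and 24 months post-intervention". Table 1 schedules weight at baseline and at those four visits (t1 to t4) and at no other time.

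Under Primary analysis method, a repeated measures model compares the mean count of criteria between the randomised groups over time. The listed adjustments are age, co-morbidities, prescribed medicines, cardiovascular health and energy intake. The baseline frailty score is not among them.

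**The concern.** A change score is interpretable only if the same thing is measured at both ends. Here one item in five moves from recalled, unintentional loss over a full 12 months to measured loss over whatever interval the trial weights allow. That interval is short at the first follow-up and longer later. The item can therefore fall after baseline and rise again later while nobody's weight behaviour changes.

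What is at stake is the reading of the trial's central question, whether pre-frail people improve, hold or progress. A drop within an arm at t1 could be taken for reversal of frailty, and a later rise for progression, when part of each comes from the definition. Analysing change from baseline also carries a differently defined baseline item into the outcome, which adds noise to the comparison of arms.

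**Working it through.** No stated figure in the article bears directly on this point, so there is none to reproduce. The check sets the two rules side by side, computes the windows, and sizes the shift under stated assumptions.

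**1. The two rules**

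| | Baseline | Follow-up |
|---|---|---|
| Source | participant recall | scale weight |
| Intent | unintentional only | no condition stated |
| Threshold | more than 3 kg | at least 5% |
| Look-back | 12 months | prior year, limited by available weights |

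The thresholds coincide where 0.05 × W = 3 kg, so W = 60 kg. At 50 kg, 5% is 2.5 kg; at 80 kg it is 4.0 kg; at 90 kg it is 4.5 kg.

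**2. The windows.** Assume no wait between the baseline weight and the first class. Ten weeks is 10/52.18 × 12 = 2.3 months; eight weeks is 8/52.18 × 12 = 1.8 months. With 10 weeks:

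| Visit | Months from baseline | Longest window from a trial weight, within a year |
|---|---|---|
| t1 (0 m) | 2.3 | 2.3 (baseline) |
| t2 (6 m) | 8.3 | 8.3 (baseline) |
| t3 (12 m) | 14.3 | 12.0 (t1) |
| t4 (24 m) | 26.3 | 12.0 (t3) |

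For the baseline weight to be a year old, the wait before a 10-week programme would have to be about 6 − 2.3 = 3.7 months (for t2) or 12 − 2.3 = 9.7 months (for t1). If the two programmes ran one after the other in the combined arm (assumption, 18 weeks = 4.1 months), t2 would be about 10.1 months from baseline, still under a year.

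**3. What happens to one participant.** Someone who lost 4 kg before enrolment without trying scores 1 at baseline. With stable weight afterwards, the measured loss at t1 is zero and the item scores 0. The total falls by one criterion with no change since enrolment.

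**4. Size within an arm.** Let p be the proportion positive at baseline. The article gives no value; assume 5–20%. Assume also that the chance of meeting the item is proportional to window length. The mechanical drop is p × (1 − window/12).

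| p | Drop at t1: p × (1 − 2.3/12) | Drop at t2: p × (1 − 8.3/12) |
|---|---|---|
| 0.05 | 0.040 | 0.015 |
| 0.10 | 0.081 | 0.031 |
| 0.20 | 0.162 | 0.062 |

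**5. Between arms.** Baseline is taken before randomisation and each visit's rule is common to all arms, so the same expected drop is subtracted from every arm and largely cancels. It does not cancel exactly if t1 falls at the end of each arm's own programme, because the windows then differ a little. For 8 against 10 weeks the residue is p × (2.3 − 1.84)/12, about 0.002 to 0.008 criteria. For the assumed 18-week sequence it is p × (4.14 − 2.3)/12, about 0.008 to 0.03.

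**The case against.** The strongest reply is that the comparison of interest is between randomised arms. Assessors are blinded and the rule at each visit does not depend on the arm, so the switch is common to all groups. This stands. A reader might set the 0.04–0.16 drop against the 0.43 reduction under Sample size and conclude that much of the target effect is artefact. The documents do not support that: the first is a shift within every arm, the second a difference between groups.

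A reader might also infer that deliberate weight loss in the active arms would count as frailty and bias the result against the interventions. Nothing in the article suggests it. Senior Chef teaches cooking, menu planning and budgeting, SAYGO is an hour a week of strength and balance work, and the Background concerns poor nutritional status and maintaining weight. Nor does the article say that intentional loss counts; it states no condition. That warrants clarification, not a claim of bias.

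It can further be said that loss in the prior year may mean any loss observed within it, so at t1 and t2 the window is shortened and the rule is still usable. That is a fair reading, and the windows depend on there being no long wait before classes. It does not remove the inconsistency: a window of about 2 months is not comparable with a 12-month recall.

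Finally, one might take the absence of a FRAIL questionnaire row in Table 1 to mean that exhaustion is not measured at follow-up. The table has no such row at baseline either, where the items are certainly used, so this reflects a condensed table.

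Using measured weight where it is available is a defensible choice. The difficulty lies in analysing change across the switch.

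**Conclusion.** The point holds as a defect in the definition of the primary outcome, limited to one item of five. Change from baseline and the time profile of the five-item score cannot be read as change in frailty alone. On assumed baseline prevalences of 5–20% and yield proportional to window length, the within-arm artefact is about 0.04–0.16 criteria at t1 and 0.015–0.06 at t2. Both ranges rest on those assumptions and on a 10-week interval from baseline to the end of the programme.

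For the between-arm comparison the consequence is smaller. The shift largely cancels; what remains is added noise, not quantified here, and an item that can hardly discriminate at t1, because few people are likely to lose 5% of their weight in about 10 weeks. The documents give no ground for calling this bias in the 0.43 effect. It should be settled before the analysis, since the remedy is cheap and works with data already collected.

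**What to change.** 1. **Analyse follow-up scores, not change.** Compare the scores at t1 to t4 between arms with the baseline score as a covariate. A covariate need not be measured by the same rule as the outcome, so the switch then does no harm to the contrast.
2. **Limit the interpretation.** Do not describe within-arm change from baseline in the five-item score as reversal or progression of frailty.
3. **Add a sensitivity analysis on the four-item score** without weight loss. Grip strength, gait speed, exhaustion and physical activity have no separate baseline definition.
4. **Complete the weight-loss definition.** State the reference weight for each visit (baseline for t1 and t2) and whether intentional loss counts, and acknowledge the shorter windows at t1 and t2.

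Asking the 12-month recall question again at each follow-up looks like the natural remedy, but at t1 about 12 − 2.3 = 9.7 of its 12 months would lie before the programme. It would carry baseline positives forward and would add self-report by unblinded participants.

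The cost is a few sentences in the analysis plan and one extra analysis. No new data are needed for the covariate or four-item analyses. The short early windows remain and can only be acknowledged.
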